### 6.3. Sample size

#### Total sample: 290 patients (145 per group)

The results of an earlier study by Sprecher 1993, measuring the effect of 10.2 g of *Plantago ovata* a day in the reduction of the levels of LDL cholesterol were used to calculate the sample.

The value of the effect to be detected ( $d = 7.5$  mg/dl) is equivalent to a reduction of 5% of LDL in patients with LDL baseline values of 150 mg/dl.

The working hypothesis is:

$$H_0: \Delta \text{LDL } \textit{plantago ovata} - \Delta \text{LDL placebo} < |7.5| \text{ mg/dl}$$

$$H_1: \Delta \text{LDL } \textit{plantago ovata} - \Delta \text{LDL placebo} \geq |7.5| \text{ mg/dl}$$

Where  $\Delta \text{LDL} = \text{final LDL} - \text{baseline LDL}$

For a statistical significance of  $\alpha = 0.05$  and a power of 80%, with a standard deviation of 20 mg/dl in the  $\Delta \text{LDL}$ , the sample size required to detect significant differences of 7.5 mg/dl between the group treated with *Plantago ovata* and the group treated with placebo is 112 patients per group, for which, adjusted to an expected percentage of losses of 15%, a total of **270 patients** will be required.

After treatment, approximately 75% of the patients treated with soluble fibre (84 patients) and 85% of those treated with placebo (95) will not have 130 mg/dl of LDL-C in plasma. A statin will be added to all these patients' treatment.

It is assumed that the combination of soluble fibre with statins will cause the mean value of LDL-C to fall from 157 mg/dl to 125.6 mg/dl ( $\Delta \text{LDL}$  soluble fibre + statin = 31.4 mg/dl). In the placebo + statin group from 161 mg/dl to 136.85 mg/dl ( $\Delta \text{LDL}$  placebo+statin = 24.15 mg/dl).

For a statistical significance of ( $\alpha=0.05$ ), a power of 80%, a standard deviation in the  $\Delta \text{LDL}$  of 18.5 mg/dL and a ratio of 0.85 between groups treated with placebo for 0.75 treated with soluble fibre, **the sample size** necessary to detect differences of

7.25 mg/dl in the  $\Delta$ LDL between the group treated with statin+soluble fibre and the group treated with statin + placebo is 111 patients in the placebo group and 98 patients in the soluble fibre group.

As the percentage of failure in the objective of LDL-C equal to or lower than 130 mg/dl is 75% in the patients treated with soluble fibre and 85% in those treated with placebo, adding a 10% of patients lost to follow-up means that a **total sample of 290 patients (145 per group)** will be required.

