| $e_{it}$                | indicates residual error, where $e_{it} \sim N(0, \sigma_e^2)$                                                                               |

In order to study other variables at other post-baseline visits, when necessary, an ANCOVA model will be made for each one, analogous to that described above. The baseline homogeneity will be evaluated using a Student's *t* test for independent data.

The variation in the LDL-C concentrations for week 8 to week 16, will be measured by way of intragroup analysis using analysis methods for repeat measurements.

The level of statistical significance will be established at 0.05 bilateral.

The evaluation of the continuous secondary efficacy endpoints will be analogous with the previously described ANCOVA for the primary endpoint. The continuous secondary endpoints to be analysed are described below:

- Weight and blood pressure
- Total cholesterol, triglycerides, HDL cholesterol, apolipoproteins (apo) B-100 and A-1 and lipoprotein (a).
- The oxidation markers: alpha tocopherol and gamma tocopherol in LDL, resistance of LDL to oxidation (lag time), LDL oxidation "in vivo" and lipid lipoperoxides.
- The inflammation markers: IL-1beta, interleukin-6, TNF-alpha, amyloid-A, high sensitivity C-reactive protein, fibrinogen, leukocytes.

- The indicators of antithrombotic activity: folic acid, homocysteine, plasminogen activator inhibitor (PAI-1).
- The individual response to the plasma lipids and their modulation by apolipoprotein E polymorphisms, cholesterol ester transport protein (CETP), apolipoprotein A-V, FABP 2, ABCG5 and ABCG8, fibrinogen, fibrinogen activator inhibitor, angiotensin converting enzyme and other polymorphisms which might describe their involvement in the development of cardiovascular diseases.
- Fasting complement component 3 (C3)
- Mannose-binding lectin (MBL) activity
- Remnant-like particle cholesterol concentration (RLP-C)
- Parameters of cholesterol absorption and synthesis: plant sterols (campesterol and beta-sitosterol, reflecting cholesterol absorption) and lathosterol (reflecting cholesterol synthesis)
- Determination of atherogenic apo B-containing particles (VLDL, IDL and LDL subclasses),
- HDL particle phenotype and HDL particle composition
- Cholesterol ester transfer protein activity

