### 12.3.2 Secondary efficacy analysis.

The combined cholesterol-lowering effect of treatment with *Plantago ovata husk* and statins to achieve the therapeutic objective will be studied. The proportion of successes, i.e. the patients in whom plasma LDL-C concentrations are below 130 mg/dl following combined treatment of *Plantago ovata husk* and statins will be calculated for each treatment.

The significance of the differences between these proportions will be evaluated using the chi-squares test. The null hypothesis considered will be that the proportion of success is the same in the two treatments for a two-tailed significance level of 0.05.

The effect of the treatment of *Plantago ovata* husk fibre on blood pressure will be evaluated by analytical procedures equivalent to those conducted to evaluate the effect of *Plantago ovata* husk fibre on plasma LDL-C concentration.

The effect of the combination of statins with *Plantago ovata* husk on blood pressure will be evaluated by analytical procedures equivalent to those conducted to evaluate the effect of the combination of statins and *Plantago ovata* husk on plasma LDL-C concentration.

The effect of the polymorphisms of apolipoprotein E, the cholesterol ester transfer protein (CETP), apolipoprotein A-V and the FABP 2 on the response in plasma lipid concentrations will be made by adjusting multiple regression models over the difference in plasma LDL-C concentrations between visits.

Furthermore, possible variations in the effects of the soluble fibre and the statins according to the characteristics at the beginning of the study, LDL-C level, gender or BMI will be studied.

A multiple linear regression model will be adjusted over the difference in the plasma LDL-C concentrations between visit S8 and visit S0, where the treatment carried out and the endpoints of age, gender, BMI, or LDL-C level at visit S0 will be used as covariates.

A multiple linear regression model will be adjusted over the success proportion, i.e. patients in whom plasma LDL-C concentrations are below 130 mg/dl following the combined treatment of *Plantago ovata* husk and statins, where the treatment carried out and the endpoints of age, gender, BMI or level of LDL-C at visit S0 will be used as covariates.

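### Section 6.3 sizes the statin phase on a between-arm difference in mean LDL-C change, but section 12.3.1 analyses that change only within each arm

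*Protocol*

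**What the plan says.** Protocol section 6.3 contains two sample size calculations. The first, for fibre v placebo from S0 to S8, gives 112 per group and 270 in total after losses. The second concerns the phase in which simvastatin is added for patients who have not reached the LDL-C target. It assumes a fall of 31.4 mg/dl with fibre + statin (157 to 125.6) and 24.15 mg/dl with placebo + statin (161 to 136.85). The comparison is explicitly between arms: the size needed to detect the difference of 7.25 mg/dl "between the group treated with statin+soluble fibre and the group treated with statin + placebo is 111 patients in the placebo group" and 98 in the fibre group. Inflated for the share of patients entering the phase and for 10% lost, this gives 290, the figure adopted.

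In section 12.3.1 the between-arm ANCOVA of LDL-C is defined for the S8 minus S0 difference. For the statin phase the rule is different: "The variation in the LDL-C concentrations for week 8 to week 16, will be measured by way of intragroup analysis", using repeated-measures methods. LDL-C is not in the list of continuous secondary endpoints that receive the same ANCOVA.

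Section 12.3.2 compares the arms after combined treatment on the proportion of patients below 130 mg/dl: "The significance of the differences between these proportions will be evaluated using the chi-squares test". It adds a regression on that proportion with treatment, age, gender, BMI and S0 LDL-C.

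**The concern.** The quantity that fixes N and the analysis prescribed for that quantity do not match. Section 4.1 asks whether fibre adds to the statin effect or cancels it, and section 4.2 makes the combined effect a secondary objective. Only a contrast between randomised arms can speak to that. In the statin phase every patient receives simvastatin, so the change within one arm mixes the statin effect, any fibre effect, and regression to the mean after selection on a high S8 value. A significant fall in each arm is what one would see whether fibre helps, does nothing, or modestly interferes.

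At stake is the use of the enlarged sample. Section 6.3 recruits more patients to obtain 80% power for a mean difference, and the analysis section then gives that mean difference no estimate, confidence interval or test. Because the protocol names a method, a statistical analysis plan that followed it would carry the mismatch forward.

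**Working it through.** **Inputs (section 6.3 unless noted).** Two-sided alpha 0.05 (section 12.3.1: "The level of statistical significance will be established at 0.05 bilateral"); power 80%; difference 31.4 − 24.15 = 7.25 mg/dl; an SD of the change "of 18.5 mg/dL and a ratio of 0.85 between groups treated with placebo for 0.75 treated with soluble fibre"; failure to reach the target "is 75% in the patients treated with soluble fibre and 85% in those treated with placebo"; loss 10%.

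**1. Reproduce the statin-phase size.** With k = 0.75/0.85 = 0.882,

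n(placebo) = (1.96 + 0.8416)² × 18.5² × (1 + 1/k) / 7.25² = 7.849 × 342.25 × 2.133 / 52.56 = 109.0, which rounds up to 110.

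n(fibre) = 0.882 × 110 = 97.1. The t-based solution is 110.1 and 97.1. The protocol states 111 and 98, so the figure reproduces.

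**2. Reproduce the total.** 111/0.85/0.90 = 145.1 and 98/0.75/0.90 = 145.2, hence 145 per arm and 290 in total.

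**3. Compare with the S0 to S8 size.** 2 × 7.849 × 20² / 7.5² = 111.6, so 112 per group. Then 224/0.85 = 264, against 270 stated. The adopted 290 therefore comes from the statin-phase contrast. It adds 290 − 270 = 20 patients, about 7% of the total.

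**4. What the prescribed within-arm test would show.** With SD 18.5 for the change:

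- Fibre + statin: 31.4 / (18.5/√98) = 31.4/1.869 = 16.8.
- Placebo + statin: 24.15 / (18.5/√111) = 24.15/1.756 = 13.8.
- Fibre arm if fibre adds nothing (fall of 24.15): 24.15/1.869 = 12.9.

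Power is about 100% in every case, including the last, so the result does not distinguish a fibre effect from none.

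**5. What the sized contrast would show.** SE = 18.5 × √(1/98 + 1/111) = 2.564; 7.25/2.564 = 2.83; power = Φ(2.83 − 1.96) = 0.81 (0.80 on the t distribution).

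**6. Is the planned responder test a substitute?** Its power depends on the SD of final LDL-C, which the protocol does not give. Assuming normality and an SD of 15 to 30 mg/dl, at 98 v 111:

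| Assumed final means | SD 15 | SD 20 | SD 30 |
|---|---|---|---|
| 125.6 v 136.85 (as stated) | 99% | 90% | 57% |
| differing by 7.25 only (125.6 v 132.85) | 79% | 55% | 28% |

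It may be well or poorly powered. The 80% stated in section 6.3 does not refer to it.

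**7. Which covariate matches the sized contrast.** Section 6.3 sizes the change from the start of the statin. The stated S16 means differ by 136.85 − 125.6 = 11.25, which is 7.25 plus the 161 − 157 = 4 mg/dl difference already present at S8. A model of S16 LDL-C adjusted only for S0 would carry most of that 4 mg/dl into the estimate. With S8 as covariate and slope b, the adjusted difference is 11.25 − 4b, which equals 7.25 at b = 1. S8 is therefore the covariate closest to what was sized.

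**The case against.** The strongest reply is that a between-arm test of the combination does exist. The secondary objective is framed in terms of reaching the therapeutic target, and section 12.3.2 compares the arms on exactly that, by chi-square and by a regression with treatment as a term. This stands. A reader might infer that the protocol never compares the arms on the combination; it does, but on a binary outcome that section 6.3 did not size.

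A reader might also infer that the protocol means to judge fibre by setting two within-arm p-values side by side. It does not say so. The sentence only says how the variation will be measured. The fault is that the mean change is given no other analysis.

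Other routes can be argued. Section 12.3.1 allows an analogous ANCOVA at other post-baseline visits, and one could read the difference to S16 as a further variable. But the clause is for other variables and applies only if needed, while LDL-C from week 8 to 16 has its own explicit rule. Section 12.3.2 analyses blood pressure under the combination in the same way as LDL-C under the combination, but this only points back to analyses that contain no between-arm test of a mean. The polymorphism regressions use LDL-C differences between visits to study genotype and name no statin-phase arm contrast.

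Finally, the statin phase is secondary, and detail for it could sit in an analysis plan that is not at hand. The first part is right and limits the severity. The second would excuse silence, but the protocol is not silent: it specifies an intragroup method.

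**Conclusion.** The point holds as a mismatch between section 6.3 and section 12.3.1. N = 290 rests on a between-arm difference of 7.25 mg/dl in mean statin-phase LDL-C change. That change is assigned to a within-arm analysis that would give statistics of about 16.8 and 13.8, and about 12.9 in the fibre arm with no fibre effect at all. The between-arm responder analyses in section 12.3.2 are genuine but address a different quantity.

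It does not follow that the trial's main conclusion is at risk. Section 12.3.1 defines the primary analysis as S8 minus S0 between arms, that comparison is put at 270 patients, and 290 covers it. Section 8.1.1 places the primary endpoint at the end of intervention with fibre and statins; if that wording governed, the gap would weigh more, but the analysis section is explicit. About 20 of the 290 patients are attributable to this contrast. Severity: should be fixed.

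The statistics rest on the protocol's planning values (falls of 31.4 and 24.15, SD 18.5, 98 and 111 patients). The responder powers rest on an assumed SD of final LDL-C.

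**What to change.** In section 12.3.1, replace the intragroup sentence with a between-arm ANCOVA of the S8 to S16 LDL-C change (S16 LDL-C as outcome gives the same treatment effect), with S8 LDL-C as covariate, by assigned arm among patients entering the statin phase. Report the treatment difference with its 95% CI. Keep the within-arm changes as description only. The responder analyses in section 12.3.2 can stay.

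Add a sentence of limitation: entry to the phase is selected on S8 LDL-C, at expected rates of 75% with fibre and 85% with placebo, so this secondary comparison is made in a subset defined after randomisation and is not fully protected by it. Adjusting for S8 LDL-C reduces the imbalance in that variable but does not restore randomisation.

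The cost is one replaced sentence, one added model and the limitation. No new data are needed, because Annex 1 already schedules paired lipid profiles before S8 and S16. N does not change: with 145 per arm, 10% lost and 85% or 75% continuing, 145 × 0.90 × 0.85 = 110.9 and 145 × 0.90 × 0.75 = 97.9 patients are expected, and power for 7.25 mg/dl with SD 18.5 is about 80%.

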#### **Secondary endpoint**

- To study the combined cholesterol-lowering effect of treatment with *Plantago ovata* husk and statins to achieve the therapeutic objective.
- To analyse the effect of *Plantago ovata* husk fibre on blood pressure.
- To study the effect of the combination of statins with *Plantago ovata* husk on blood pressure.
- To evaluate whether the response on plasma lipids is modulated by the polymorphisms of apolipoprotein E, cholesterol ester transfer protein (CETP), apolipoprotein A-V and FABP 2.
- Furthermore, possible variations of the effects of the soluble fibre and the statins according to the characteristics at the beginning of the study, LDL-C level, gender or BMI will be studied.

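### N = 290 is set by a between-arm comparison of the statin-phase LDL-C change, but section 12.3.1 analyses that change only within each arm

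*Protocol*

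**What the plan says.** Protocol section 6.3 makes two sample-size calculations. The first, for the fibre phase, arrives at 270 patients. The second, for the statin phase, seeks to detect "7.25 mg/dl in the $\Delta$ LDL between the group treated with statin+soluble fibre and the group treated with statin + placebo", with "a standard deviation in the $\Delta \text{LDL}$ of 18.5 mg/dL", 80% power and alpha 0.05. It requires 111 placebo and 98 fibre patients. After allowing for the share of patients who enter the phase and for 10% losses, it arrives at 290, which is the trial's N.

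Section 4.2 lists as the first secondary objective "To study the combined cholesterol-lowering effect of treatment with" the fibre and statins, in order to reach the therapeutic target.

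Section 12.3.1 specifies a between-arm ANCOVA for LDL-C, with the outcome defined as the difference between S8 and S0. For LDL-C from week 8 to week 16 it says that the variation "will be measured by way of intragroup analysis using analysis methods for repeat measurements". The analogous ANCOVA at later visits is offered for other variables, when needed, and for a list of continuous secondary endpoints that does not contain LDL-C.

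Section 12.3.2 adds a chi-square test comparing the two treatments on the proportion with LDL-C below 130 mg/dl after combined treatment, and a regression on that success outcome with treatment as a covariate.

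**The concern.** The quantity that fixed the number of patients is not the quantity that the analysis section compares between arms. In the second phase both arms receive simvastatin from S8. A within-arm change from S8 to S16 therefore contains the statin effect in each arm, and a significant fall in the fibre arm says nothing about whether fibre contributed.

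Two large, highly significant within-arm falls could be reported as support for the combination when the contrast that justified raising N from 270 to 290 was never tested. This is not a detail left open for a later analysis plan: the protocol names a method, and that method does not match its own sample-size section.

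**Working it through.** **Inputs.** From section 6.3: difference 7.25 mg/dl, SD of change 18.5 mg/dl, alpha 0.05, power 80%, fibre-to-placebo ratio 0.75/0.85 = 0.882, evaluable 98 (fibre) and 111 (placebo), entry shares 75% and 85%, losses 10%. Assumed means: 157 to 125.6 mg/dl with fibre + statin (fall 31.4), 161 to 136.85 mg/dl with placebo + statin (fall 24.15). Two-sided testing comes from section 12.3.1: "The level of statistical significance will be established at 0.05 bilateral".

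**Step 1: which comparison sets N.**

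Placebo n by the normal approximation = (1.96 + 0.842)² × 18.5² × (1 + 1/0.882) / 7.25² ≈ 109.03, rounded up to 110, with 97 in the fibre arm. The t-based calculation gives 110.06, rounded up to 111, and 111 × 0.882 ≈ 98. These are the stated figures.

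- Placebo: 111 / 0.85 / 0.90 = 145.1 randomised
- Fibre: 98 / 0.75 / 0.90 = 145.2 randomised

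That gives 145 per group and 290 in total, as stated. The fibre phase alone (7.5 mg/dl, SD 20) needs 112 per arm. With 15% losses this is 112 / 0.85 ≈ 132 per arm, or 264, against 270 stated. So the statin-phase between-arm comparison determines N.

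**Step 2: what the within-arm analysis would show.** The statistic is change / (18.5 / √n).

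| Situation | Calculation | Result |
|---|---|---|
| Fibre + statin, as planned | 31.4 / (18.5/√98) | 16.8 |
| Placebo + statin, as planned | 24.15 / (18.5/√111) | 13.8 |
| Fibre + statin, if fibre adds nothing | 24.15 / (18.5/√98) | 12.9 |

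Power is essentially 100% in every row. A within-arm fall of only about 5 mg/dl would already be detected with 80% power: 2.80 × 18.5/√98 = 5.2 and 2.80 × 18.5/√111 = 4.9. The within-arm result is therefore the same whether or not fibre has an effect.

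**Step 3: what a between-arm test would show.** The standard error of the difference is 18.5 × √(1/98 + 1/111) = 2.56, and 7.25 / 2.56 = 2.83. This corresponds to about 80.7% power by the normal approximation. With only the 84 fibre and 95 placebo patients that section 6.3 derives from 112 per arm, power would be 74.4%. The added patients serve this contrast.

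**Step 4: whether the binary analysis replaces it.** On the protocol's means, final LDL-C differs by 136.85 − 125.6 = 11.25 mg/dl. Of this, 161 − 157 = 4 mg/dl is already present at S8, so the proportion below 130 mg/dl mixes the fibre-phase effect with what happens during the statin phase. Its power depends on the SD of final LDL-C, which the protocol does not give. Assuming normally distributed values and an SD of 15 to 30 mg/dl, power with 98 and 111 patients runs from about 99% down to 58%.

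**The case against.** The strongest reply is that the combined phase does have a between-arm test. A reader might infer from the intragroup sentence that the first secondary objective gets no LDL-C comparison at all. The documents do not support that. The objective is worded in terms of reaching the therapeutic target, and section 12.3.2 tests precisely the proportion below 130 mg/dl between treatments and adds a regression with a treatment term. This stands, and it narrows the point to the continuous change. It does not remove the point, because the binary endpoint did not set N and does not isolate the statin-phase change.

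A second reply is that the analogous ANCOVA for other variables at other visits could be read to cover an S16 difference in LDL-C. That reading is possible but weak. The sentence is conditional, LDL-C is absent from the endpoint list that follows, and LDL-C from week 8 to 16 has its own sentence, which says intragroup.

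A reader might also infer that blood pressure under the combination is analysed only within arms, because section 12.3.2 ties it to the procedures used for the combination's effect on LDL-C. That cross-reference names no procedure, and section 12.3.1 lists blood pressure among the endpoints for the ANCOVA. The text is unclear rather than wrong.

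It is tempting to add that selection on a high S8 value inflates each within-arm fall through regression to the mean. The direction is plausible, but its size would need a measurement SD that the protocol does not give, and the argument does not need it.

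Finally, the primary S8 minus S0 comparison is untouched by all this, and 290 exceeds the 270 stated for it.

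**Conclusion.** The mismatch is real and should be corrected. The between-arm difference of 7.25 mg/dl in the S8 to S16 LDL-C change determines N = 290, yet section 12.3.1 assigns that change to a within-arm analysis, which would be highly significant in both arms (about 16.8 and 13.8 standard errors) and would remain so in the fibre arm with no fibre effect (about 12.9). These figures rest only on the protocol's own means, common SD and evaluable numbers.

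The conclusion is limited to the continuous LDL-C change in the statin phase. It does not extend to the primary analysis, to the between-arm analyses of the proportion below 130 mg/dl, or to a claim that blood pressure lacks a between-arm model.

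**What to change.** Replace the intragroup sentence in section 12.3.1 with wording to this effect: the S16 minus S8 change in LDL-C (each the mean of the two determinations in the preceding week) will be compared between arms by ANCOVA with a treatment term and S8 LDL-C as covariate, giving the adjusted difference and its 95% confidence interval; within-arm changes from S8 to S16 are descriptive.

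Use S8, not the pre-randomisation value, as the reference. Final LDL-C adjusted for the D-10/D-7 baseline would target the 11.25 mg/dl contrast, not the 7.25 mg/dl that section 6.3 sized.

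State that the comparison is restricted to patients with S8 LDL-C of at least 130 mg/dl. Section 6.3 expects 75% of the fibre arm and 85% of the placebo arm to qualify. This is selection after randomisation, so the comparison is not fully randomised and should be reported as such.

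For blood pressure under the combination, say in section 12.3.2 that the between-arm ANCOVA listed in section 12.3.1 applies.

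The cost is one paragraph of statistical wording. The data are already scheduled, and 290 patients give about 80% power for the restored comparison on the protocol's assumptions.
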